**Fig. 1 Fig1:**
[figure not shown]
**a** The study area, **b** The study area

This water, sanitation and hygiene (WASH) project has been designed to reduce diarrhea among children under four by providing clean water, improving household latrines and promoting relevant hygiene practices. Since the construction and use of latrines by household members cannot be fully achieved without necessary behavioral changes, hygiene promotion was included as one of the activities under the project.

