### Study design

This cluster-randomized trial takes a *quartier*, a subdivision of a village, as the randomization unit since well-equipped latrines have an impact on diarrhea transmission across households at a cluster level. A “well-equipped latrine” is defined as having (1) a pit with a depth of more than 1.5 m; (2) a superstructure; (3) a roof; (4) a cement slab; (5) a pit-hole cover; and (6) a hand-washing facility based on the UNICEF Healthy Village Programme in the DRC. Any latrine that does not meet a single requirement will not be defined as a well-equipped latrine in the trial. A *quartier* is the lowest administrative unit in the DRC, where the number of households ranges from 396 to 2873. All the interventions will be undertaken on a *quartier*-wide basis. Since the purpose of the intervention is to reduce diarrhea, a *quartier* will be an appropriate dimension for the transmission zone, where humans, vectors, and intermediate hosts are interacting with each other and sharing a common pool of parasites.

We will employ a phase-in design. For well-equipped latrines, the project will roll out only in an intervention arm for the first phase (8 months). A total of four rounds of household surveys (including the baseline survey) will be conducted every 6 months (June 2015, January and August 2016, and February 2017) throughout the trial. The second round of the survey will be conducted immediately before the control arm will receive the intervention for the next 6 months. After the intervention period, we will have a follow-up period of about 1 year in which the third and the fourth survey will be conducted.

A preliminary survey was conducted from March through May of 2013 to gather information and analyze conditions at the field level to develop the WASH project in the DRC. On the basis of the preliminary results, each *quartie*r was rated by the degree/intensity/severity of the needs in terms of quantity of safe water per person per day *(liter/person/day),* distance to water points from the *quartier* (*km*), and the percentage of households with a household latrine (%).

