### Project implementation

KECO will be responsible for supervision and management of the project implementation. Two sanitation experts have been deployed to this project team from the WSA to provide technical advice and three sanitation officials from SNHR have been seconded to facilitate community mobilization and provide information about the local culture, such as social norms and, if any, taboos during the project period.

Before the intervention, WASH committees were established right after 18 *quartiers* had been selected for the target area of the water supply program in February 2015; therefore, the committees were present in both the intervention and control arms. Nine WASH committee members were elected by the people living in each *quartier*. It was recommended that they elect at least three female members, but several *quartiers* could not recruit at least three female members to form their committee. The main roles and responsibilities of the WASH committee with regard to the water supply program are to maintain water facilities and collect water fees from the *quartier* residents. Later on, after 9 *quartiers* were selected for this sanitation intervention, we added new roles and responsibilities of the committee for latrine improvement for the intervention group and trained the committee members to perform those tasks. The new roles and responsibilities of the WASH committee are defined as (1) community mobilization on latrine improvement; (2) educating community people for healthier hygienic practices; (3) drawing and regularly updating the Sanitation Map; (4) monitoring the progress, especially on the ‘recording status of the Sanitation Calendar’ and ‘latrine improvement situation’ at the household-level in each *quartier*.

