The degree of latrine improvement will be scored according to the well-equipped latrine criteria. This will allow us to assess whether and how the diminishing effect of well-equipped latrines on diarrhea incidence among children under four differs depending on the degree of latrine improvement. Previous studies [14, 15] exploring the health benefits of sanitation have not paid attention to the possibility that the effect of latrines might vary depending on the degree of their improvement. Although a recent trial [21] reported an increase in access to one’s own latrine from 33 to 64.8% in rural Mali, they found no effect of a community-led sanitation improvement on the children’s diarrhea. Based on the 5-f theory, the Joint Monitoring Programme defines an “improved sanitation facility as one that hygienically separates human waste from human contact,” highlighting the importance of accounting for improvement status of latrines. In the case of pit latrines, the existence of a slab and hand-washing facilities, pit-hole depth and number of flies could be considered criteria for identifying the improved status of latrines. Applying these criteria, the proportion of improved latrines in Pickering et al. (i.e., latrines with concrete slabs) would be reduced to less than 30%. Focusing solely on the presence or access to any latrine type may mask the genuine health benefits of improved latrines.

The study hypothesis was not disclosed to people subject to the trial, though the general objectives were explained to them when obtaining informed consent. Thus, people are highly unlikely to be aware of the arm to which they belong because the sanitation intervention will continue to be executed in the control arm during the second phase. We thus surmise that the underreporting of diarrheal prevalence among the caregivers with a household latrine will not be a serious problem in this study. However, the limitation of not blinding still remains in this study since having a latrine is explicit in itself and many of the WASH committee members in the control arms were aware of the intervention even from the beginning due to their participation in the community lottery activity for random allocation.

Since the trial’s randomization process yielded remarkably balanced results between the two arms, and since no other intervention is expected to roll out until February 2017, any differences observed in diarrheal incidence can be attributable to latrine improvement.

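### The randomised contrast is well-equipped latrines plus hygiene education and mobilisation, so a difference between arms cannot be credited to latrine improvement alone

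*Protocol article*

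**What the plan says.** All places are in the protocol article.

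- **Discussion.** The attribution rests on two premises: that randomisation gave balanced arms, and that "no other intervention is expected to roll out until February 2017". From these it concludes that "any differences observed in diarrheal incidence can be attributable to latrine improvement".
- **Background.** The stated aim is to find how far well-equipped latrines reduce child diarrhea.
- **Study design.** A well-equipped latrine has six parts: pit depth, superstructure, roof, cement slab, pit-hole cover and hand-washing facility. The latrine programme goes to the intervention arm first. The second survey falls just before the control arm starts.
- **Study setting.** The project is meant to reduce diarrhea through safe water, better latrines and hygiene promotion. The section adds that "hygiene promotion was included as one of the activities under the project".
- **Project implementation.** Committees were formed in all 18 quartiers when these were chosen as "the target area of the water supply program". After the nine sanitation quartiers were selected, "we added new roles and responsibilities of the committee for latrine improvement for the intervention group", and members were trained for these roles. The first role is mobilisation for latrines. The second, listed separately, is "educating community people for healthier hygienic practices".

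**The concern.** The attribution names one cause, while the intervention group is described as receiving something further that could lower diarrhea by another path. Education in hygienic practice can change hand-washing, food handling or the care of a sick child in a household whose latrine has not changed. If it is delivered only where latrines are promoted, its effect is included in the difference between arms and would be reported as a latrine effect.

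This matters for the trial's purpose. The Background criticises earlier work for seldom isolating the net effect of sanitation, and the Discussion expects the result to guide how resources for sanitation are allocated. A reader who takes a package effect for a hardware effect could expect the same benefit from building latrines without the education.

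**Working it through.** No figure in the plan depends on this point, so the check compares what the sections say.

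1. **What differs by arm in phase one.** According to Project implementation, the intervention group has latrine mobilisation and hygiene education. According to the Intervention arm description in the Discussion and the subsidy rules in Project implementation, it also has the subsidised latrine materials, hand-washing facility included. The control arm is to receive the programme later.

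2. **What counts as latrine improvement.** The six criteria in Study design are all physical. The hand-washing facility is the sixth, so an effect through that facility is a latrine effect on the document's own terms. Hygiene education meets none of the six criteria and lies outside the definition.

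3. **Whether the design can separate the two.** As the roles are written, the intervention arm has both latrines and hygiene education in phase one, and the control arm has neither. With two arms and two components that always go together, only their joint effect is identified.

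4. **Whether the two premises help.** Baseline balance concerns the state of the arms before treatment. Even perfect balance would not separate components delivered together afterwards. The absence of outside projects removes outside causes but leaves the project's own hygiene education in place.

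5. **Whether the planned analyses help.** The secondary question in the Background relates latrine components to diarrhea as an association, and the Discussion scores the degree of latrine improvement. Neither is a randomised comparison, and the listed components are the physical parts and upkeep of the latrine, with no measure of education.

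6. **Whether education had room to act.** In Table 1, hand-washing after cleaning a child was 6.7% in the intervention arm and 8.2% in the control arm, so 100 - 6.7 = 93.3% and 100 - 8.2 = 91.8% did not report it. After handling a sick person the figures were 17.6% and 14.3%. The room is large, although this does not show that practice will change.

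7. **Whether the role is confined to the intervention arm.** The text is not consistent. Project implementation lists hygiene education among roles added for the intervention group. The same list contains drawing the Sanitation Map, which the Discussion says is updated in both arms, and monitoring the Sanitation Calendar, which goes to every registered household. Study setting describes hygiene promotion without naming an arm.

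**The case against.** The best defence is that hygiene promotion is a means of delivery. Study setting says it was included because people will not build and use latrines without changing behaviour, and Project implementation describes the new roles as being for latrine improvement. Any trial of high coverage needs mobilisation, and randomisation still gives a valid effect of what was delivered. The disputed text is one sentence in the Discussion, not an analysis rule. This stands in part: the fault lies in the label of the effect. But the education role is wider than latrine uptake, and Study setting itself lists hygiene as a separate route to less diarrhea.

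A reader might infer more than the document supports in three ways.

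- **The hand-washing facility as an added intervention.** It is inside the definition of a well-equipped latrine. It shows only that the effect is not one of excreta containment alone.
- **The water programme as a confounder.** It targets all 18 quartiers, and nothing shows that it differs by arm.
- **The statement about other interventions as false.** Eligibility criteria and enrollment excludes quartiers with other WASH projects scheduled, and the Discussion sentence can be read the same way, as meaning outside projects. It needs qualifying and should not be deleted.

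It is also fair that the control arm's exposure to hygiene education is unsettled. If both arms receive the same education in phase one, it does not differ between them. The contrast would then be latrines and mobilisation on top of education, and the text should say so.

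**Conclusion.** The point holds as a matter of what the trial may conclude. As the intervention is described, a difference between arms in phase one estimates the combined effect of well-equipped latrines (with their hand-washing facility), hygiene education and mobilisation, against delayed roll-out. The Discussion assigns it to latrine improvement, which the design does not support.

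This rests on reading Project implementation as written, with hygiene education as a new role for the intervention group only. The document gives no basis for dividing an effect between its parts, so no size can be attached. A reader might infer that the randomised comparison is biased. It is not: the intention-to-treat comparison and the sample size are untouched by this point, and only the name given to the effect changes.

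**What to change.** 1. Reword the Discussion conclusion and the aim in the Background to the combined effect of well-equipped latrines, hygiene education and mobilisation compared with later roll-out.
2. Qualify the statement on other interventions: no outside WASH project is expected, and the project's own water programme covers both arms.
3. Reconcile Study setting, Project implementation and the Discussion on which hygiene activities, and which of the listed committee roles, the control arm has in phase one.
4. Report the hand-washing practice variables of Table 1 by arm at the second survey, the last one before the control arm starts. This shows how far practice diverged; it does not divide the effect.

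The cost is some rewording and one table from a survey already planned. The downside is a less specific conclusion: the trial would speak for the package and not for latrines alone.

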### Primary health outcome

The primary outcome of the study is reduction in diarrheal incidence (cases per 1000 child-week), prevalence and average duration (days per episode) in children under four. To measure progress, the mother or caregiver of each household will record the diarrheal episodes of the youngest child under four on a daily basis using the ‘Sanitation Calendar’ (Fig. 4). The Sanitation Calendar will enable us to look into the intervention’s effects on incidence density as well as the duration of diarrhea in children under four. A 7-day recall period will be used to measure diarrheal prevalence.

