### Health outcomes assessment, sanitation calendar

The incidence of the diarrhea of the youngest child under four will be recorded by the mother or caregiver on the Sanitation Calendar distributed to each registered household in early August, 2015. The mother or caregiver will be educated to mark ‘O’ whenever her youngest child under four has diarrhea and mark ‘X’ on each day without diarrhea over the next 12-month period of longitudinal observation. Mothers were informed of the definition of diarrhea - three or more of watery stools in 24 h, with pictures of various stool types produced by the World Health Organization.

Households will be monitored by the WASH committee twice a month and instructed to keep recording appropriately. We employed the diary methodology to overcome the limitations reported in previous studies, such as recall bias [29] and reporting fatigue, leading to underestimation [30]. The diary methodology will allow us to capture more precisely the effects of well-equipped latrines on the duration of diarrhea and diarrheal incidence density. As an incentive for keeping a diary, the project has made the Sanitation Calendar a voucher, which can later be exchanged with a gift. During the monthly monitoring visit, the WASH committee will check the status of diary recording by taking a photo of the Sanitation Calendar marked as ‘O’ or ‘X’ for each day of each month.

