For this trial, keeping the Sanitation Calendar is crucial to documenting the progress toward the primary endpoint. A supervisory visit to the WASH committee will be made at least twice every month to encourage the mother or caregiver to record diarrheal incidence on a daily basis, in an unbiased manner. On this visit, the WASH committee will photograph the Sanitation Calendar to confirm whether it is being kept well, which will be verified by supervisors’ (WSA and SNHR sanitation experts) direct observations during the randomly sampled household visit. During the early stage of the intervention, in July and August 2015, strong emphasis will be placed on the importance of appropriately recording outcomes in the Sanitation Calendar. Accordingly the supervisory visit to randomly sampled households will be strengthened to help people get accustomed to recording in the Calendar in a desirable manner. The WASH committee will convene a community meeting to review the Sanitation Calendar on a regular basis and significant errors, if any, will be corrected.

Considering the alternative sanitation policies evaluation result [31], the non-discriminative distribution of material subsidies contingent upon voluntary preparation of some materials for latrine improvement and a commitment of labor may increase the uptake of well-equipped latrines within a short time period, with a strong social multiplier by increasing the ownership. This trial is expected to provide valuable information on the resource allocation of sanitation improvement by determining the effects of improved sanitation on diarrheal reduction for children. The findings of this study will be relevant to populations where improved water and sanitation coverage is minimal.

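### Committees that are not blind to arm review the Sanitation Calendars at community meetings and errors are then corrected, which leaves the record behind incidence and duration open to later change

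*Protocol article*

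**What the plan says.** **The calendar's role.** Under Primary health outcome, the calendar is to "enable us to look into the intervention’s effects on incidence density as well as the duration of diarrhea in children under four". The third component has another source: "A 7-day recall period will be used to measure diarrheal prevalence". The Discussion says that "keeping the Sanitation Calendar is crucial to documenting the progress toward the primary endpoint".

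**The correction step.** The same Discussion paragraph states: "The WASH committee will convene a community meeting to review the Sanitation Calendar on a regular basis and significant errors, if any, will be corrected". It does not say what counts as an error, who makes the change, on what evidence, or which version is analyzed.

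**Who runs the review.** Under Project implementation, after the intervention quartiers were chosen, "we added new roles and responsibilities of the committee for latrine improvement for the intervention group and trained the committee members to perform those tasks". Fourth among these added roles is one that begins "monitoring the progress, especially on the" and goes on to name calendar recording and latrine improvement together. For the other arm, the Discussion concedes that "many of the WASH committee members in the control arms were aware of the intervention even from the beginning".

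**Checks on the record.** Under Health outcomes assessment, "the WASH committee will check the status of diary recording by taking a photo of the Sanitation Calendar" at the monthly visit. The Discussion adds that supervisors from the two implementing bodies (WSA and SNHR) verify calendars by observation at randomly sampled households.

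**The concern.** The diary was chosen to avoid recall bias. A mark that is changed later at a meeting is recall again, now in a public setting convened by a body that, in the intervention arm, also promotes latrines. Residents are to be taught that latrine coverage protects the community, so those present may expect less diarrhea where latrines have been built.

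The Discussion treats every day not marked O as a day without diarrhea. A withdrawn O therefore becomes a healthy day. Depending on which days change, the effect falls on the episode count, on the duration, or on both. A change can also go the other way, from X to O. If changes were more frequent, or leaned in a different direction, in one arm, they would create or hide an effect on incidence and duration. The final data set would not show it unless the original marks had been kept. The article expects no difference in reporting between arms but does not consider corrections.

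**Working it through.** The plan states no figure on this point. The check is a reading of the text, followed by an illustration of scale.

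**1. Does the text allow entries to change?** The object of the review is the calendar, and errors found are to be corrected. The sentence is passive and may partly mean correcting how mothers record. Nothing in it excludes changing past marks.

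**2. Are those who review blind?** No. Intervention committees were trained for the latrine work. In the control arm the article says many members were aware, not all.

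**3. Do the checks preserve the original?** The committee itself takes the photographs, to confirm that the calendar is being kept. They are not named as the analysis record, and their timing relative to the meetings is not fixed, so a mark changed before the photograph would leave no trace. Supervisors see only a sample of households. For latrine status the Discussion recognizes information and courtesy bias among committee members and has supervisors judge improvement from the photographs. It gives no such rule for the calendar marks.

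**4. Scale, under an assumed rate.** Let f be the share of episodes removed in one arm only, with no true effect. The documents give no f. The control rate is λ₀ = 0.10 per child-week (Sample size calculation), so the other arm shows λ₁ = 0.10 × (1 − f):

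- f = 5%: 0.095, an apparent 5% reduction, or 5/25 = 20% of the planned effect
- f = 10%: 0.090, an apparent 10% reduction, or 40% of it
- f = 20%: 0.080, an apparent 20% reduction, or 80% of it

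**5. False-positive chance.** The article's variance terms are used with y = 540 child-weeks per quartier and 9 quartiers per arm:

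SE² = [(λ₀ + λ₁)/y + k²(λ₀² + λ₁²)]/9, Z = (λ₀ − λ₁)/SE, chance = Φ(Z − 1.96) + Φ(−Z − 1.96).

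For f = 10% and k = 0.0633: SE² = [0.19/540 + 0.00401 × 0.0181]/9 = 0.0000472, SE = 0.00687, Z = 1.456, chance ≈ 0.31. With f = 0 the formula returns 5%.

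| f | k = 0.063 | k = 0.20 | k = 0.30 |
|---|---|---|---|
| 5% | 11% | 7% | 6% |
| 10% | 31% | 15% | 10% |
| 20% | 85% | 48% | 29% |

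The article uses k = 0.063 and also k = 0.3. The middle value is √0.000401/0.1 = 0.20, from its variance estimate and its definition of between-cluster variance as k²λ².

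**6. How many marks is that?** At y = 540 a quartier has 540 × 0.1 = 54 episodes, and 10% is 5.4. The Discussion puts duration at 10–20 days, so removing them entirely means changing about 54 to 108 daily marks per quartier.

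**The case against.** **The sentence may not mean editing data.** The sentences before it concern regular, unbiased recording and helping people to get used to the calendar. This stands as a reason not to say that entries will be altered. It does not remove the permission that the wording gives.

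**Review may be the same in both arms.** A reader might infer from Project implementation that calendar review happens mainly in the intervention arm. The documents do not support that. The same list of added roles includes the Sanitation Map, which the Discussion says is updated in both arms. Calendar monitoring under Health outcomes assessment is not limited by arm, and neither are the meetings.

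**The reward is not a motive.** A reader might also infer that committees gain by removing O marks. The reward is for 80% coverage with well-equipped latrines, not for low diarrhea. Nor does the text say that only the mother could know the child's state: a caregiver may also record.

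**Large one-sided change is demanding.** Removing whole episodes would take many mark changes in all nine quartiers of one arm and none in the other, despite photographs and supervisor visits. This is a fair reason to treat the larger values of f as extreme.

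**Correction rules may lie in the full protocol.** They may. The point rests on a procedure that the article does state, and states as open-ended.

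**Conclusion.** The point holds as a weakness in how primary outcome data are protected. The article describes a route by which calendar entries can be changed after the fact, in meetings run by people who are not blind to arm, with no provision that the original mark is kept or is the one analyzed. It touches incidence and duration, not 7-day prevalence.

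It would be too strong to conclude that the outcome will be edited differently by arm, or that a bias of a given size should be expected. The documents state neither, and the size depends wholly on the assumed f. If 5% to 20% of episodes were removed in one arm only, the spurious reduction would be 5% to 20%, with a false-positive chance between about 6% and 85% depending on f and k. The procedure should be changed because the protection is cheap and the harm, if it occurred, could not be detected afterwards.

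**What to change.** Replace the correction sentence with a rule along these lines:

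- Calendars are photographed before any community meeting, and the marks as first photographed are the primary analysis record.
- Any later change is logged with date, reason, original value and arm.
- The number of changes is reported by arm, and corrected entries enter a sensitivity analysis only.
- Meetings deal with how to record, without changing individual marks, and follow the same schedule in both arms.

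The cost is wording, field instructions and a simple log, since the photographs are already planned. If field work has ended (the last survey was set for February 2017), the analysis part can still be applied where photographs known to precede a meeting exist.

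The downside is that some genuine marking errors stay in the primary data, including diarrhea days that a mother forgot to mark and that therefore count as X. The sensitivity analysis with corrected entries shows how much this matters.
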